# Special orthopaedic geriatrics (SOG) - a new multiprofessional care model for elderly patients in elective orthopaedic surgery: a study protocol for a prospective randomized controlled trial of a multimodal intervention in frail patients with hip and knee replacement

**DOI:** 10.1186/s12891-022-05955-w

**Published:** 2022-12-09

**Keywords:** Orthogeriatric, Orthogeriatric co-management (OGC), Geriatric, Total hip arthroplasty (THA), Total knee arthroplasty (TKA), Elderly patients, Frailty, Multiprofessional care, Perioperative Care of Older Persons (POPS), Comprehensive geriatric assessment (CGA)

## Abstract

**Background:**

Due to demographic change, the number of older people in Germany and worldwide will continue to rise in the coming decades. As a result, the number of elderly and frail patients undergoing total hip and knee arthroplasty is projected to increase significantly in the coming years. In order to reduce risk of complications and improve postoperative outcome, it can be beneficial to optimally prepare geriatric patients before orthopaedic surgery and to provide perioperative care by a multiprofessional orthogeriatric team. The aim of this comprehensive interventional study is to assess wether multimorbid patients can benefit from the new care model of special orthopaedic geriatrics (SOG) in elective total hip and knee arthroplasty.

**Methods:**

The SOG study is a registered, monocentric, prospective, randomized controlled trial (RCT) funded by the German Federal Joint Committee (GBA). This parallel group RCT with a total of 310 patients is intended to investigate the specially developed multimodal care model for orthogeriatric patients with total hip and knee arthroplasty (intervention group), which already begins preoperatively, in comparison to the usual orthopaedic care without orthogeriatric co-management (control group). Patients ≥70 years of age with multimorbidity or generally patients ≥80 years of age due to increased vulnerability with indication for elective primary total hip and knee arthroplasty can be included in the study. Exclusion criteria are age < 70 years, previous bony surgery or tumor in the area of the joint to be treated, infection and increased need for care (care level ≥ 4). The primary outcome is mobility measured by the Short Physical Performance Battery (SPPB). Secondary outcomes are morbidity, mortality, postoperative complications, delirium, cognition, mood, frailty, (instrumental) activities of daily living, malnutrition, pain, polypharmacy, and patient reported outcome measures. Tertiary outcomes are length of hospital stay, readmission rate, reoperation rate, transfusion rate, and time to rehabilitation. The study data will be collected preoperative, postoperative day 1 to 7, 4 to 6 weeks and 3 months after surgery.

**Discussion:**

Studies have shown that orthogeriatric co-management models in the treatment of hip fractures lead to significantly reduced morbidity and mortality rates. However, there are hardly any data available on the elective orthopaedic care of geriatric patients, especially in total hip and knee arthroplasty. In contrast to the care of trauma patients, optimal preoperative intervention is usually possible.

**Trial registration:**

German Clinical Trials Register DRKS00024102. Registered on 19 January 2021.

**Supplementary Information:**

The online version contains supplementary material available at 10.1186/s12891-022-05955-w.

## Background

According to the United Nations (UN), the number of people aged 65 and older in Germany and worldwide will continue to rise in the coming decades [1]. In 2060, about 30% of the population in Germany will be over 65 years old and about 11% over 80 years old [2]. This demographic shift, along with improvements in general living standards, healthcare, nutrition and education, is leading to a steady increase in geriatric patients undergoing major surgeries [3, 4]. It is expected that the number of elderly patients with the need for elective orthopaedic surgery will continue to rise significantly. For example, the number of primary total hip and total knee arthroplasties (THA and TKA) is expected to increase by 71 and 85% respectively by 2030 [5].

However, the orthogeriatric patient is not a standard patient for whom the usual orthopaedic care is sufficient. Comorbidities, polypharmacy, frailty, osteosarcopenia, malnutrition, immobility, cognitive impairments and other geriatric syndromes as well as increased complication and mortality rates are typical for geriatric patients [6–8]. To address this challenge and improve care of elderly patients, centers have increasingly emerged in traumatology in recent years in which elderly patients are treated jointly by trauma surgeons and geriatricians. Orthogeriatric co-management (OGC) plays an important role especially in frail patients with hip and other fragility fractures today. Many studies have shown that orthogeriatric co-management models lead to significantly reduced morbidity and mortality rates in patients with hip fractures [9–14]. In addition, comprehensive geriatric care promoted functional improvement in older patients with hip fracture [15–17]. However, the models are country-specific and structurally different [18]. The transfer of these care models to other trauma-related conditions (spinal injuries or pelvic fractures) and their scientific investigation through studies is very limited so far [9, 19, 20].

In elective orthopaedic surgery, orthogeriatric co-management models are still less established. Only few studies have investigated the effect of OGC in the context of elective orthopaedic surgery [21]. However, the number of geriatric patients is increasing not only for hip fractures, but also for elective orthopaedic surgery, especially total joint replacement. Based on the favourable data in geriatric traumatology in the care of hip fractures, it is imperative to develop specific orthogeriatric co-management models for patients with total hip and knee arthroplasty and to investigate their benefits for patients. In contrast to the emergency treatment of hip fractures, a major advantage here can be the longer time for optimal preoperative preparation (prehabilitation). A randomized, blinded trial has shown that personalized prehabilitation in patients prior to elective major abdominal surgery significantly improves the physical performance of patients and also reduces postoperative complications by more than 50% [22]. Already at this stage, the geriatrician should examine the patient, a comprehensive geriatric assessment (CGA) should be done and appropriate preoperative interventions (API) should be arranged.

### Objectives and research hypothesis

The aim of our trial is to assess the effectiveness of comprehensive orthogeriatric care (SOG care model) versus standard orthopaedic care with treatment by orthopaedic surgeons only in patients undergoing primary THA and TKA. The SOG care model consists of a comprehensive geriatric assessment, appropriate preoperative intervention, fast-track surgery principle and multimodal perioperative care on a SOG unit. We examine the outcomes of randomly assigned patients with assessments on postoperative days 1 to 7, 4 to 6 weeks and 3 months after surgery. Because immobility is an immediate result of osteoarthritis (OA) and leads to long-term functional deterioration, we choose mobility as the primary outcome. The current report outlines the research design and protocol for evaluating this randomized controlled trial of a multimodal intervention in frail patients with hip and knee replacement.

We hypothesize that multimodal perioperative orthogeriatric co-management (SOG care model) can improve the mobility of patients with total hip and knee arthroplasty (measured by SPPB).

The objectives of the randomized controlled trial are.The primary objective is to examine the impact of comprehensive geriatric assessment, appropriate preoperative intervention, fast-track surgery principle and multimodal perioperative care on a SOG unit (SOG care model) versus standard care after total hip and knee arthroplasty on mobility on postoperative day 3 and 7, 4 to 6 weeks and 3 months after surgery.The secondary objectives are to explore potential efficacy of the comprehensive geriatric assessment, appropriate preoperative intervention, fast-track surgery principle and multimodal perioperative care on a SOG unit (SOG care model) versus usual orthopaedic care after total hip and knee arthroplasty on overall health, disability, morbidity, mortality, postoperative complications including delirium, cognition, mood, frailty, activities of daily living/instrumental activities of daily living, malnutrition, pain, polypharmacy, PROM and PREM on postoperative day 1 to 7, 4 to 6 weeks and 3 months after surgery.The tertiary objectives are to test the effect of comprehensive geriatric assessment, appropriate preoperative intervention, fast-track surgery principle and multimodal perioperative care on a SOG unit (SOG care model) versus standard care after total hip and knee arthroplasty on length of hospital stay, readmission rate, reoperation rate, transfusion rate and time to rehabilitation.

In addition, within the framework of the study, we aim:4.To develop and validate a new screening tool (SOG screening) for geriatric patients undergoing elective orthopaedic surgery.5.To develop and validate a routine preoperative laboratory test for orthogeriatric patients.

## Methods/design

### Study design

The SOG study is a registered, monocentric, prospective, randomized controlled trial. This parallel group RCT with a total of 310 patients is intended to investigate the specially developed multimodal care model (SOG care model) for orthogeriatric patients with total hip and knee arthroplasty (intervention group), which already begins preoperatively, in comparison to the usual orthopaedic care without orthogeriatric co-management (control group). The study data will be collected preoperative, postoperative day 1 to 7, 4 to 6 weeks and 3 months after surgery. The duration of the study was originally planned for 3 years. Due to the Corona-19 pandemic, an extension to 3.5 years is expected to be necessary. The trial is registered at the German Clinical Trials Register and the registry platform for international clinical trials of the World Health Organization (WHO) under the same Main ID DRKS00024102. We used the Standard Protocol Items: Recommendations for Interventional Trials.

(SPIRIT) guidelines to guide the reporting of our trial protocol [23]. A SPIRIT Checklist is provided as Additional file 2, and a flow diagram is included as Fig. 1.

**Fig. 1 Fig1:**
[figure not shown]
Standard Protocol Items Recommendations for Interventional Trials (SPIRIT) Schedule of enrolment, interventions, and assessments. SPPB: Short Physical Performance Battery, ADL: Activities of Daily Living, IADL: Instrumental Activities of Daily Living, MMSE: Mini-Mental State Examination, GDS: Geriatric Depression Scale, NRS: Nutritional Risk Screening, NU-DESC: Nursing Delirium Screening Scale, PROM: Patient Reported Outcome Measurement, WOMAC: Western Ontario and McMaster Universities Osteoarthritis Index, EQ-5D: Euroquol Quality of Life Index, PREM: Patient Reported Experience Measurement, PPP33: Perioperative Patient Questionnaire, ISAR: Identification of Seniors at Risk, SOG: Special Orthopaedic Geriatrics

### Study setting

The study will be conducted at the Orthopaedic Department of Regensburg University Center, Asklepios Klinikum Bad Abbach, Germany. Here, about 18,000 patients are treated per year in the university outpatient clinic and > 1500 endoprosthetic procedures on the hip and knee joints are performed annually. Participants are recruited at the university outpatient clinic if they have a diagnosis of primary hip or knee osteoarthritis and an indication for THA or TKA. Preoperative interventions will be provided after randomization in written form or by telephone by the research nurse and/or geriatrician to the patient/family doctor/specialist. Pre-op exams and interventions can also be performed on-site at the university outpatient clinic. After surgery, the patients in the intervention group are treated in a special orthogeriatric ward (SOG unit) and the patients in the control group are treated in an ordinary orthopaedic ward of the orthopaedic university hospital.

### Eligibility criteria

Patients (or a representative) must provide written, informed consent before any study procedures occur. Included participants should fulfil the following inclusion criteria: primary hip or knee osteoarthritis, an age ≥ 70 years and multimorbidity or an age ≥ 80 years, with an indication for elective unilateral hip or knee replacement. The waiting time until surgery must be at least 4–6 weeks. Exclusion criteria: Age < 70 years, previous bony surgery or tumour in the area of the joint to be treated, acute infection and increased need for care (care level ≥ 4).

### Sample size

The sample size calculation is based on the primary endpoint of the analysis - “Improvement of Mobility”, measured by Short Physical Performance Battery (SPPB). According to previous studies, the clinically relevant difference between the two groups is conservatively estimated at 0,5 points with an expected standard deviation of 1,48 points [24]. Due to a 1:1 randomization, the number of cases per group is 139 to achieve a power of 80% at a 5% significance level (Gpower). Taking into account a possible dropout rate of 10%, a total of 310 patients should to be randomized.

The patient is not informed about the result of the randomization. The allocation is only known to the team directly treating the patient. In particular, the investigators who perform the post-intervention testing are blinded. For the patients, blinding is ensured by the fact that the patients in the control group also receive physiotherapy after surgery. Furthermore, the planned length of stay in hospital is the same for both study groups. An interdisciplinary ward round is simulated, but without orthogeriatric care in the actual sense. Very rare circumstances that may lead to emergency intervention during the study, and therefore possibly emergency unblinding, may include unpredictable highly pathological, life-threatening assessment, examination or laboratory results.

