### Data analysis

The evaluation is carried out as an intention-to-treat analysis. Baseline demographic and clinical characteristics of the participants will be described using summary statistics (means, standard deviations and frequencies). Significance in differences will be tested using t-test for continuous variables with normal distribution, chi-square test for categorical variables and Mann-Whitney U-test for continuous variables with non-normal distribution. Normality of the distributions will be tested graphically. We will examine the difference preoperatively and postoperatively (3 days, 7 days, 4–6 weeks, 3 months) with regard to the primary outcome variable (SPPB score) in the intervention and control group, as well as between the groups (postoperatively). To assess significance in differences we will use paired-samples t-test. Although the random assignment of the patients should provide unbiased results, the need for an adjusted analysis will be considered. To this end, in order to account for potential confounders, we will consider general linear models (e.g. multivariate linear regression and analysis of covariance [42] to evaluate between-group differences in SPPB scores. The need for an adjusted analysis within generalized linear (mixed) models will be considered as well. Secondary endpoints will be analysed both descriptively and standardized within adjusted regression analyses. *P*-values *p* < 0,05 will be considered as statistically significant. Detailed sensitivity analyses are planned for all outcomes of the intervention. Potentially missing data will be completed using adapted techniques (e.g. multiple imputation).

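### The sample size does not say whether 0.5 points and SD 1.48 describe change in SPPB or a postoperative score, and no between-arm primary model is fixed, so the stated 80% power is tied to no defined comparison

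*Protocol article*

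**What the plan says.** The Sample size section of the protocol article bases the calculation on a primary endpoint labelled "Improvement of Mobility", measured by the SPPB. It says that "the clinically relevant difference between the two groups is conservatively estimated at 0,5 points", "with an expected standard deviation of 1,48 points". It gives no time point and does not say whether the SD belongs to a change or to a single score. The result is 139 per group and, after 10% dropout, 310 randomised.

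The Data analysis section looks at the SPPB before and after surgery within each arm, "as well as between the groups (postoperatively". The one test it then names for this is a paired t-test. On adjustment it says "we will consider general linear models (e.g. multivariate linear regression and analysis of covariance", with mixed models also only under consideration. Baseline SPPB is not named as a covariate.

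The Primary outcome section defines the outcome as the SPPB itself. It is measured on admission, on days 3 and 7, at 4–6 weeks and at 3 months. The Study setting section places the preoperative interventions after randomisation, so the admission SPPB follows them.

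**The concern.** Improvement ordinarily means a change from before to after. Change appears in the analysis only within arms, and the between-arm comparison is described as postoperative. The SD of a change and the SD of a score are different quantities unless the correlation between the two measurements happens to be 0.5. An SD that is tied to neither cannot show that the planned comparison has the stated power.

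The named test adds to the gap. A paired t-test cannot compare two independent arms, and the 139 comes from a two-sample calculation. With adjustment left to be considered, the article does not settle whether the primary result will be a raw score, a change or an adjusted score. That choice could be made after the data are seen.

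**Working it through.** **Inputs.** From Sample size: difference 0.5, SD 1.48, power 80%, alpha 5%, 1:1 allocation, 10% dropout. Assumed, because the article does not give them: a two-sided test; correlation ρ between preoperative and postoperative SPPB from 0.3 to 0.8; equal SDs before and after surgery; and the same 0.5-point difference whichever quantity is compared.

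**The plan's own figure.** For a two-sample t-test with standardised difference 0.5/1.48 = 0.338, the noncentral t gives 138.5, hence 139 per arm, and power at 139 is 80.1%. A one-sided test would need only about 110 per arm, so the two-sided reading is the one that reproduces. Dropout: 139/0.9 = 154.4, hence 155 per arm and 310 in total. Both stated figures are correct.

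**If 1.48 is the SD of a postoperative score.** The sized quantity is the compared quantity, and power is 80.1% as stated.

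**If 1.48 is the SD of change.** With equal SDs, SD(change) = SD(score) × √(2(1−ρ)). So SD(score) = 1.48/√(2(1−ρ)). At ρ = 0.7, for example, this is 1.48/√0.6 = 1.91, and the standardised difference is 0.5/1.91 = 0.262.

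| Assumed ρ | SD of score | Power at 139 per arm | n per arm for 80% |
|---|---|---|---|
| 0.3 | 1.25 | 91% | 100 |
| 0.4 | 1.35 | 87% | 116 |
| 0.5 | 1.48 | 80% | 139 |
| 0.6 | 1.65 | 71% | 173 |
| 0.7 | 1.91 | 58% | 231 |
| 0.8 | 2.34 | 43% | 345 |

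The break-even is where 2(1−ρ) = 1, that is ρ = 0.5. Below it the postoperative comparison has more than the stated power, above it less.

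**The difference of 0.5 is open in the same way.** If the preoperative intervention raises SPPB by the time of admission, the between-arm difference in change from admission equals the postoperative difference minus that early gain. The 0.5 then also means different things on the two scales.

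**The case against.** The strongest reply is that the mismatch rests on one word. The label can be loose wording for better mobility: the effect size is stated as a difference between two groups, the Primary outcome section defines the outcome as the SPPB itself, and the Data analysis section calls the primary variable the SPPB score. On that reading 1.48 is a score SD and the power is as stated. This stands as a possible reading. The article does not confirm it, and the source cited for the SD is not available to settle it.

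Secondly, the analysis section mentions ANCOVA and regression, and earlier an ordinary t-test, so the postoperative comparison need not be unadjusted; the details may sit in an analysis plan. This stands in part. However, the ordinary t-test follows the description of baseline characteristics and is not tied to the SPPB. The test that is tied to it is the paired one, which does not fit two independent arms. That is stated in the article, not left out of it.

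Three stronger readings are tempting and are not supported:

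- **That the trial is underpowered.** This needs both a change SD and a correlation above 0.5, and the article establishes neither.
- **That power falls to 66% or 73%.** Those values arise at ρ = 0.3 and 0.4 if 1.48 is a score SD and the arms are compared on change (SD 1.48 × √1.4 = 1.75 and 1.48 × √1.2 = 1.62). No between-arm test of change is stated.
- **That adjusting for baseline SPPB would secure 80% under either reading.** This holds only with an SPPB taken before randomisation. The screening described in the article includes none, and with recruitment running since April 2021, patients already randomised may have no such value.

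**Conclusion.** The point holds as a defect of definition. The sample-size arithmetic is correct, but the 80% is attached to no stated between-arm comparison: the SD is unspecified, the endpoint label suggests change, the arms are compared postoperatively, the named test is paired, and adjustment is optional.

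The effect on power is conditional. There is none if 1.48 is a score SD. If it is a change SD, power runs from about 91% down to 43% over assumed correlations of 0.3 to 0.8, and is at or above the stated level for correlations up to 0.5. These figures rest on equal SDs at both times and on a correlation range that the article does not supply. It should be corrected because correction is cheap and closes the choice of primary result before the data are seen.

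**What to change.** **Data analysis section.** For the between-arm primary analysis, replace the paired t-test and the conditional wording on adjustment with one committed linear model. The outcome is SPPB at one named primary time point. The terms are arm, the randomisation strata (sex; hip or knee) and covariates already recorded at screening before randomisation, such as age. Within-arm paired comparisons can remain as description.

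**Sample size section.** State that 0.5 and 1.48 refer to that comparison. If the source shows that 1.48 is the SD of change, restate the power with a postoperative-score SD and give the correlation assumed.

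**Admission SPPB.** Do not adjust for it, or take change from it, in the primary model. It is measured after randomisation and after the preoperative intervention, so it could absorb part of the effect.

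**Cost.** Wording in the protocol and analysis plan, settled before any analysis by arm. No extra patients are needed for this change and no new measurement: an added screening-visit SPPB is not required.

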### Recruitment strategy

After the orthopaedic surgeons have assessed the patients referred for hip or knee problems in the university outpatient clinic and have given the indication for elective primary THA or TKA, the patient is presented to the research assistant and the geriatrician after checking the eligibility criteria. There will be a detailed explanation of the study with written informed consent. The research assistant assists the geriatrician in reviewing comorbidities and polypharmacy, and in conducting the Identification of Seniors at Risk (ISAR) screening [25], SOG screening and Nutritional Risk Screening (NRS) [26]. There is also a physical examination by the geriatrician and a laboratory test. Clinic administrators assign patients a surgery date in 4–6 weeks at the earliest or place patients on the surgery waiting list and assign them a surgery date later.

